### Intervention

In the current trial the surgical procedure is standardised to achieve a better comparability of the outcome. For each surgical intervention a Polytetrafluoro-ethylene vascular prostheses from the same manufacture (PTFE prostheses, thin walled, diameters 4-10 mm) will be surgical implanted in accordance with the standard practice of the investigative centre using a non-absorbable polypropylene suture material USP 5-0, USP 6-0 for the anastomotic suture line. The investigator will perform the distal anastomosis first. The clamp will be opened to check for suture hole bleeding. If bleeding occurs, the clamp will be closed and a randomization envelope containing the study material will be opened. The devices will be cut into half. Thereafter, the clamp at the distal anastomosis will be removed and a stopwatch will be started and the randomized device will be placed circumferentially around the anastomosis and applied for three minutes. The suture line is monitored by the investigator and the time required to achieve complete sealing is recorded with a stopwatch. If haemostasis is not achieved after 3 minutes a new equal device is placed around the anastomosis for another 2 minutes and the time to obtain haemostasis is measured with a stopwatch. In the case that suture hole bleeding has not stopped after 5 minutes the investigator will wait for another 5 minutes to achieve haemostasis. Subjects are considered treatment failures if suture hole bleeding could not be controlled within 10 minutes or if additional interventions are required to achieve sealing. Every application of a new device will be recorded with type of device and time after clamp removal.

If haemostasis is achieved at the distal anastomosis the surgeon will perform the proximal anastomosis. Following the anastomotic procedure the clamp at the prosthesis is released. If suture hole bleeding is present, the clamp will be closed. The device according to the randomization procedure will be prepared (if no bleeding at the distal anastomosis had occurred, the randomization envelop has to be opened) and the clamp will be removed and a stopwatch will be started. The randomized device will be placed circumferentially around the proximal anastomosis and applied for three minutes. If haemostasis is not achieved after 3 minutes a new equal device is placed around the anastomosis for another 2 minutes and the time to obtain haemostasis is measured with a stopwatch. In the case that suture hole bleeding has not stopped after 5 minutes the investigator will wait for another 5 minutes to achieve haemostasis. Subjects are considered treatment failures if suture hole bleeding could not be controlled within 10 minutes or if additional interventions are required to achieve sealing. Every application of a new device will be recorded with type of device and time after clamp removal. After achieving haemostasis at the proximal anastomosis the proximal clamp will be removed and the surgical procedure will be finished.

### Study Device

The investigational products are the haemostats Lyostypt and Surgicel (= Tabotamp). For Lyostypt, the size 5 cm × 8 cm and for Surgicel, the size 5 cm × 7,5 cm will be supplied to the study centre.

### Lyostypt

Lyostypt is an absorbable wet-stable collagen compress made of collagen fibrils of bovine origin. Collagen leads to thrombocyte adhesion and to activation of coagulation factor XII. Lyostypt collagen haemostatic fleece is indicated for capillary bleedings, parenchymal haemorrhages, oozing wound haemorrhages, for the local haemostasis in haemodialysis and as a supportive method for other techniques in haemostasis. Lyostypt achieves haemostasis very swiftly, it can be removed easily, it can be applied endoscopically and it can be combined with fibrin glue and antibiotics (16). Collagen haemostats showed low tissue reaction, fast resorption and good biocompatibility (15). Lyostypt is y-sterilized.

### Surgicel/Tabotamp

Surgicel absorbable haemostat is a sterile absorbable knitted fabric prepared by the controlled oxidation of regenerated cellulose. The fabric is white with a pale yellow cast and has a faint caramel-like aroma. It is strong and can be sutured or cut without fraying. After Surgicel has been saturated with blood, it swells into a brownish or black gelatinous mass which aids in the formation of a clot, thereby serving as a haemostatic adjunct in the control of local haemorrhage. When used properly in minimal amounts Surgicel haemostat is absorbed from sites of implantation with practically no tissue reaction.

Surgicel is used adjunctively in surgical procedures to assist in the control of capillary, venous and small arterial haemorrhage when ligation, suturing or other conventional methods of control are impractical or ineffective.

### Sample size

The study is planned in a two-step design. Initially, 28 patients will be enrolled and a test at the α_1 _= .0102 will be performed. The exact number will depend on the number of bleeding anastomoses, as patients will be accrued until 56 applications of a randomized device have been recorded. The main test will be carried out as a parameter test in the model outlined in section statistical analysis.

The trial will be stopped for rejection of the null hypothesis if the one-sided p-value is lower than α_1_, and stopped for futility if it is higher than .50. The level of significance for the final analysis is set to α_2 _= 0.00380/p_1_, where p_1 _is the p-value corresponding to the one-sided test of the primary criterion from the interim analysis, following the approach of Bauer and Köhne [17]. For the second part of the trial, the sample size will be recalculated and will lie between 12 and 72.

This procedure maintains the overall significance level of 2.5 per cent and a power of the one-sided test as described in statistical analysis at 80 per cent. This result was obtained by simulation based on 300 replicates.

### Statistical Analysis

The primary criterion is the time to haemostasis at an anastomosis. For the evaluation of the primary criterion, the single anastomosis is treated as the observational unit. Time to haemostasis, which will be censored at 10 minutes, will be included as the response parameter in an accelerated failure time regression model [18] assuming a Weibull distribution for bleeding time with the following explanatory parameters included: treatment on anastomosis (Lyostypt vs. Surgicel), treatment on opposite anastomosis (Lyostypt vs. Surgicel), site of anastomosis (proximal vs. distal), and center. Subject will be included as a shared frailty term with lognormal distribution. The formal null hypothesis to be tested at a level of α = 0.025 (spent over two tests carried out in different stages) is: "Anastomosis bleeding time under Lyostypt is at least as long as under Surgicel".

Haemostasis during 5 and 10 minutes, local and general complication rate till 30 ± 10 days after surgery, the number of used haemostatic devices minus one will be modelled in a logistic mixed regression model using the same covariates as for the main model. Subject will enter the analysis as a random effect. If model instabilities occur due to overspecification (signified by a condition number of the design matrix of more than 40), the term "treatment on opposite anastomosis" and possibly the center effect will be dropped.

The intraoperative efficacy rating scale of each device will be modeled separately for the 4 step ranking scale of adhesion and the 5 step ranking scale of handling, using a logistic mixed model of ordinal responses using the same covariates as in the main model as fixed and surgeon and subject as random effects. Postoperative mortality will be described individually in the final report. Adverse events which are recorded will be reported casuistically, mentioning the haemostypt actually applied at the distal and proximal site.

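### The primary model adjusts distal bleeding times for a proximal device not yet in place, and estimating that term cancels the precision gained from two anastomoses per patient

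*Protocol article*

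**What the plan says.** In the protocol article, Statistical Analysis, "the single anastomosis is treated as the observational unit". The accelerated failure time model takes as covariates "treatment on anastomosis (Lyostypt vs. Surgicel), treatment on opposite anastomosis (Lyostypt vs. Surgicel), site of anastomosis (proximal vs. distal), and center". The opposite-device term is a single two-level covariate that applies to both sites. Correlation between the two anastomoses of a patient is handled as follows: "Subject will be included as a shared frailty term with lognormal distribution". On the response, the section says "Time to haemostasis, which will be censored at 10 minutes".

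The Intervention section fixes the order of events. "The investigator will perform the distal anastomosis first", and its device is applied and its bleeding timed. Then: "If haemostasis is achieved at the distal anastomosis the surgeon will perform the proximal anastomosis". A device is used only where a site bleeds. For the proximal site, "If suture hole bleeding is present, the clamp will be closed" and the assigned device is prepared. The section also provides for patients whose distal site stays dry: "if no bleeding at the distal anastomosis had occurred, the randomization envelop has to be opened".

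The Randomization section assigns each patient one of four device combinations in equal numbers. A rule in Statistical Analysis, placed with the secondary logistic models, allows the opposite-device term to be dropped if the condition number of the design matrix exceeds 40. Those secondary models reuse the covariates of the main model.

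**The concern.** A distal time is complete before the proximal anastomosis exists, so the proximal device cannot have influenced it. The only effect in time order is carry-over from the distal site to the later proximal one. The section on clinical site and safety aspects rules out a systemic effect of either device, which gives little reason to expect even that. A common coefficient averages an impossible effect on distal rows with a possible one on proximal rows.

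The cost is precision. Half of the patients receive different devices at their two sites, and the comparison within these patients should be the most precise part of the design. Once an opposite-device effect must be estimated as well, this comparison no longer identifies the treatment effect alone. The same model supplies the stage 1 test, the futility decision, the first-stage p-value that sets the final level, and the second-stage sample size.

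**Working it through.** **The plan's own figure.** The Sample size section gives a stage 1 level of 0.0102, a futility bound of 0.50, a product constant of 0.00380 and an overall one-sided level of 2.5%. The overall level is 0.0102 + 0.0038 × ln(0.50/0.0102) = 0.0102 + 0.0038 × 3.892 = 0.02499. It reproduces. The stated 80% power cannot be rebuilt, because no effect size, Weibull shape or frailty variance is given.

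**Inputs.** From the article: 28 patients, 56 applications and four combinations in equal numbers, hence 7 patients each. Assumed: both sites bleed in every patient, log time is treated linearly with total variance σ², and the within-patient correlation is ρ. The article gives no ρ.

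**Model as written.** Let β be the own-device effect and γ the opposite-device effect, with devices coded 0/1.

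- The patient sum has variance 2σ²(1+ρ) and slope β+γ on the number of sites given the test device (0, 1, 1, 2). The sum of squares about the mean is 14, so Var(β+γ) = 2σ²(1+ρ)/14 = σ²(1+ρ)/7.
- The patient difference has variance 2σ²(1−ρ) and slope β−γ on the device difference (0, 1, −1, 0). The sum of squares is again 14, so Var(β−γ) = σ²(1−ρ)/7.
- The two estimates are uncorrelated and β is half their sum. Var(β) = ¼ × σ²[(1+ρ) + (1−ρ)]/7 = σ²/14 = 0.0714σ², whatever ρ is.

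For 56 unrelated anastomoses, 28 per device, the variance is 2σ²/28 = 0.0714σ². It is the same number, so the gain from pairing is zero.

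**No opposite-device term (γ = 0).** Both contrasts estimate β. Their information adds to [7/(1+ρ) + 7/(1−ρ)]/σ² = 14/[σ²(1−ρ²)], so Var(β) = σ²(1−ρ²)/14.

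**Term on proximal rows only.** With devices centred at ±½, one patient's information, in units of 1/[σ²(1−ρ²)], is 1/2 for β, 1/4 for the carry-over effect and −ρ/4 between them. Eliminating the carry-over effect leaves 1/2 − ρ²/4 for β. Hence Var(β) = 2σ²(1−ρ²)/[28(1−ρ²/2)].

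| Assumed ρ | As written | Proximal rows only | Saving | No term | Saving |
|---|---|---|---|---|---|
| 0.2 | 0.0714 | 0.0700 | 2% | 0.0686 | 4% |
| 0.4 | 0.0714 | 0.0652 | 9% | 0.0600 | 16% |
| 0.5 | 0.0714 | 0.0612 | 14% | 0.0536 | 25% |
| 0.6 | 0.0714 | 0.0557 | 22% | 0.0457 | 36% |

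At ρ = 0.5, the 28 patients under the written model do the work of 28 × 0.0612/0.0714 ≈ 24 under proximal-only coding, or 28 × 0.0536/0.0714 ≈ 21 without the term.

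**Check in the censored Weibull frailty model.** With an assumed log-scale of 0.6, frailty SD of 0.9 and median of 3 minutes (ρ about 0.58, 12% censored at 10 minutes), the simulated SD of the log time ratio is 0.310 as written, 0.285 with proximal-only coding and 0.257 without the term. The variance savings are 1 − (0.285/0.310)² = 15% and 1 − (0.257/0.310)² = 31%. The linear formulas give 20% and 34% at ρ = 0.58, so the approximation is somewhat generous but right in direction and order of size.

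**The drop rule.** The balanced single-centre design matrix (intercept, own device, opposite device, site) has a condition number of 3.7. Even if the rule is read as covering the primary model, it would not remove the term.

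**The case against.** The strongest defence is that nothing here harms validity. The opposite-site device is itself randomised and balanced against the own-site device, so adjusting for it neither biases the treatment coefficient nor inflates the type I error. That stands.

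A reader might infer that the trial is underpowered. If the 80% belonged to a model without the term, the written model would have about 73% power at ρ = 0.4 and 68% at 0.5 (fixed design, one-sided 0.025). The Sample size section, however, ties the 80% to the test described in Statistical Analysis. On its wording that is the model with the term, so the loss may already be included. No shortfall is shown.

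A reader might also infer that patients who bleed at one site only must be lost from the primary test or miscoded. The text does not establish this. Each patient is randomised to a device for both sites, so an assigned value exists even when one site stays dry. Which value to use is a coding detail that an article may leave to the full plan.

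Finally, the timing argument does not reach every secondary model. Complications up to 30 ± 10 days arise after both devices are in place, so an opposite-site effect is possible in time there.

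What remains untouched is the mismatch between the covariate and the order of surgery, and the precision it costs.

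**Conclusion.** The point holds as a loss of efficiency in the primary model. On distal rows the opposite-device term represents an effect that the stated procedure makes impossible. Estimating it as one common coefficient removes the whole precision gain from within-patient correlation; this is exact in the balanced, complete, linear case and approximate under the censored Weibull frailty model.

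The size depends on a correlation that the article does not give: it is negligible at about 0.2 and material from about 0.4. The larger savings (25% at ρ = 0.5) belong to dropping the term altogether; keeping a carry-over term on proximal rows recovers 14%. The finding does not show bias, an inflated error rate or power below 80%. It is a free improvement, best made before the interim data are analysed.

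**What to change.** In the primary time-to-haemostasis model, set the opposite-device term to zero on distal rows. Keep it on proximal rows only, as distal-to-proximal carry-over, coded by the device applied distally, with a level for none when the distal site did not bleed. Alternatively, drop the term from the primary model and report the carry-over version as a sensitivity analysis.

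Use the same coding for the secondary outcomes measured during the timed application at each site: haemostasis by 5 and 10 minutes, and number of devices. Do not carry it over to complications up to 30 ± 10 days.

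Rerun the power simulation with the revised model and state the frailty variance assumed.

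The cost is a sentence or two in the analysis section, one recoded variable and a repeat of the simulation. No new data are needed.

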### Design

This is a randomized, controlled, prospective study to evaluate the haemostatic effect of Lyostypt versus Surgicel in arterial bypass anastomoses.

In this study, 28 eligible patients with a peripheral arterial bypass following peripheral vascular reconstruction, will be treated with the investigational devices during the pilot phase. There will be 4 treatment groups: Group 1 and 2 will receive both products one at the distal and the other at the proximal anastomosis. In group 3 and 4 the same haemostat will be applicated at both anastomoses either Lyostypt or Surgicel. The proximal bypass anastomosis will be randomized for the application of the haemostat. After discharge from the hospital the investigator will examine the patients at 30 ± 10 days after surgery (figure 1 and table 1).

**Table 1 T1:** Flow Chart COBBANA Trial.

	**Visit 1 (Screening)**	**Visit 2 (OP)**	**Visit 3 (2 ± 1 days post OP)**	**Visit 4 (Day of discharge)**	**Visit 5 (30 ± 10 Days post OP)**
Patient information	X				

Informed consent	X				

Demographic data*	X				

Smoker/non-smoker	X				

Inclusion/exclusion	X				

Past medical history	X				

Physical examination	X	X	X 1)	X 1)	X 1)

Surgery		X			

Time to obtain hemostasis		X			

Deviation from surgical procedures as described in the protocol		X			

Number of used devices		X			

Intraoperative handling of the devices		X			

Recurrence of bleeding		X	X	X	x

Adverse Event/Serious Adverse Event		X	X	X	X

Local and general complication/re-operation		X	X	X	X

Mortality					X

* date of birth, gender, weight, height,

1) of the operational wound

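### General complications, one outcome per patient, are assigned to an anastomosis-level logistic model with a subject random effect that cannot be estimated meaningfully for them

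*Protocol article*

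**What the plan says.** All of this is in the Statistical Analysis section of the protocol article unless noted.

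- The unit of analysis is fixed for the primary endpoint only: "For the evaluation of the primary criterion, the single anastomosis is treated as the observational unit".
- The main-model covariates are "treatment on anastomosis (Lyostypt vs. Surgicel), treatment on opposite anastomosis (Lyostypt vs. Surgicel), site of anastomosis (proximal vs. distal), and center". The first three are properties of an anastomosis, not of a patient.
- For several secondary endpoints, the plan then states that "local and general complication rate till 30 ± 10 days after surgery, the number of used haemostatic devices minus one will be modelled". The method named is mixed logistic regression, and its covariates are those of the primary model. On clustering it adds: "Subject will enter the analysis as a random effect".
- If the model is unstable, "signified by a condition number of the design matrix of more than 40", the opposite-site treatment term is dropped, and possibly centre. No other term is named.
- Under Design, "Group 1 and 2 will receive both products one at the distal and the other at the proximal anastomosis"; groups 3 and 4 have one device at both sites. Under Randomization, the four combinations occur equally often.

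General complications also appear in the objectives, the secondary endpoint list and the visit table. Nowhere does the article tie a general complication to an anastomosis or give it a patient-level model. Mortality, also a patient-level outcome, is only to be described individually.

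**The concern.** The model presupposes two records per patient, each with its own outcome, device and site. A general complication supplies one outcome with no site. The analyst must either keep one record per patient, where the site and own-device terms lose their meaning, or copy the outcome to two records, where the pairs always agree. In both cases the stated model has no usable answer, and whatever is reported depends on how the data were laid out and where the software stopped. At stake is the device comparison for one secondary safety endpoint.

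**Working it through.** The plan gives no figure on this point to reproduce.

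**Inputs.** 28 pilot patients and 56 device applications (Sample size); four combinations in equal numbers (Randomization), so 28/4 = 7 per combination. The article gives no complication rate. For illustration I assume 6 of 28 patients with an event: 1 of 7 with Lyostypt at both sites, 2 of 7 with Lyostypt proximal only, 1 of 7 with Lyostypt distal only, 2 of 7 with Surgicel at both sites. Bleeding at both anastomoses is assumed in all 28.

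**Coding A: one row per patient.**
- Site is the same for every row and is aliased with the intercept: rank 3 for 4 columns (intercept, own device, opposite device, site), condition number about 4e16.
- With site removed by hand, the subject SD is still not identified. The maximised log-likelihood is -14.117 at SD 0, 1, 2, 5 and 10, while the distal-device coefficient moves from -0.88 (SD 0) to -5.10 (SD 10). A random intercept on a single binary outcome only rescales the coefficients and slightly alters the shape of the link.

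**Coding B: outcome copied to both rows.** Write the two linear predictors of a patient with proximal device p and distal device d as

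- proximal row: α + a·p + b·d + c
- distal row: α + a·d + b·p

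Replacing (α, a, b, c) by (α+c, b, a, -c) merely exchanges the two predictors. Both rows carry the same outcome, so the likelihood is unchanged. A unique maximum must therefore satisfy a = b and c = 0: no site effect, and no distinction between own and opposite device. In 980 simulated data sets (25% event rate assumed, subject effect set to zero), the largest |c| was 5e-16 and the largest |a - b| was 8e-16.

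Log-likelihood of the illustration, maximised at fixed subject SD:

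| Subject SD | Log-likelihood | Each device coefficient |
|---|---|---|
| 0 | -28.67 | -0.43 |
| 2 | -21.77 | -0.70 |
| 10 | -15.98 | -2.61 |
| 40 | -14.74 | -10.06 |
| 80 | -14.54 | -19.99 |

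It rises at every step. At SD 0 each patient counts twice; as the SD grows, the second copy adds nothing, so the value tends to about -28.67/2 = -14.33. There is no finite maximum, and the coefficients drift with the SD.

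**Does the instability rule catch it?**
- Coding B: the condition number is 3.7 without a centre term and 4.4 with two assumed centres. Both are below 40, so the rule is silent.
- With a single centre (the present position under Current status), a retained centre column is constant and would trigger the rule. It would then drop opposite-site treatment and perhaps centre, and keep the subject effect. I refitted the example without opposite-site treatment, and the log-likelihood still rises at every step up to SD 80.
- Coding A: the rule triggers, but it does not name the aliased site term or the subject effect.

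The rule looks only at the fixed-effect columns, so it cannot detect a failure in the random effect.

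**A patient-level model works.** One row per patient, with proximal and distal device as covariates and no site or subject term, gives finite coefficients and a log-likelihood of -14.117. It rests on 28 independent outcomes, not 56.

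**The case against.** **What the other side can say.** The article does not define a general complication, so one value per patient is a reading, though the natural one. The sentence bundles several endpoints, and the model suits most of them: haemostasis within 5 and 10 minutes, extra devices, and local complications at a known anastomosis. Safety does not hang on this model alone. Adverse events are reported individually with the device at each site, mortality is described individually, and the safety section adds the incidence of events in the bypass region. All of that stands and limits the consequence. It does not rescue the model, because the article names this outcome, these covariates and this random effect.

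**Stronger readings that the documents do not support.**

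1. *Copied rows make the standard error 29% too small (factor 1.41).* This requires the subject effect to be removed, which the plan does not do, and even then it does not hold for the own-device coefficient. On the linear scale that coefficient equals half the difference between the both-Lyostypt and both-Surgicel means. Its true variance is (1/4)(2σ²/7) = σ²/14, and the naive 56-row variance is σ²(1/28 + 1/28) = σ²/14, the same. Only the sum of own and opposite effects is affected: true 2σ²/7 against naive σ²/14 + σ²/14 = σ²/7, a ratio of √2 = 1.41. A logistic simulation (200 patients, assumed 25% event rate, no device effect) agrees: empirical SD 0.236 against reported SE 0.233 for own device, and 0.471 against 0.331 for the sum. The plan does not name that sum as its test.

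2. *Half the patients carry no device information, leaving 7 against 7.* The counts of 14 mixed-device patients and 7 against 7 assume 28 patients who bleed at both anastomoses. Under Intervention a device is applied only where bleeding occurs, and under Sample size accrual continues until 56 applications, so the counts can differ. Even then they describe only the both-Lyostypt against both-Surgicel contrast. Groups 1 and 2 do inform the separate proximal and distal effects (14 against 14 each). What stands is that a general complication in a patient who received both devices cannot be attributed to one of them.

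**Conclusion.** The point holds for general complications and for any rate that combines them with local ones. The model as stated fails under either data layout: with one row, site is aliased and the subject variance is not identified; with copied rows, the site effect is 0, the two device effects are identical and the subject variance is unbounded. The instability rule does not repair it. This rests on general complications being recorded once per patient. The event count affects the illustrative figures but not the reasoning.

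A reader might infer that reported standard errors would be 29% too small, that half the sample is uninformative, or that the trial's safety evaluation as a whole is compromised. The documents support none of these. This is a defect in one secondary safety analysis that should be corrected; the primary test and its two-stage level are untouched.

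**What to change.** - Analyse general complications, and any combined local-and-general rate, with one record per patient and no site term or subject random effect. Take as exposure either the number of Lyostypt-treated anastomoses (0, 1, 2) or the proximal and distal devices as two factors. Choose one in advance.
- Use a method suited to few events, such as Firth or exact logistic regression.
- Tabulate the events by the four treatment groups, and state how many patients actually received a device at one site only.
- Keep the anastomosis-level mixed model for local complications that can be attributed to a specific anastomosis, and say in the text that it is confined to these.
- State that the condition-number rule does not address failure of the random effect, and name what is done if the subject variance cannot be estimated.

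The cost is analysis wording only: no change to design, data collection, sample size or the primary test. It will also show openly how little the pilot can say about patient-level safety.
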